# Prospective, randomized, double-blind, multi-center, Phase III clinical study on transarterial chemoembolization (TACE) combined with Sorafenib^® ^versus TACE plus placebo in patients with hepatocellular cancer before liver transplantation – HeiLivCa [ISRCTN24081794]

**DOI:** 10.1186/1471-2407-8-349

**Published:** 2008-11-26

## Abstract

**Background:**

Disease progression of hepatocellular cancer (HCC) in patients eligible for liver transplantation (LTx) occurs in up to 50% of patients, resulting in withdrawal from the LTx waiting list. Transarterial chemoembolization (TACE) is used as bridging therapy with highly variable response rates. The oral multikinase inhibitor sorafenib significantly increases overall survival and time-to-progression in patients with advanced hepatocellular cancer.

**Design:**

The HeiLivCa study is a double-blinded, controlled, prospective, randomized multi-centre phase III trial. Patients in study arm A will be treated with transarterial chemoembolization plus sorafenib 400 mg bid. Patients in study arm B will be treated with transarterial chemoembolization plus placebo. A total of 208 patients with histologically confirmed hepatocellular carcinoma or HCC diagnosed according to EASL criteria will be enrolled. An interim patients' analysis will be performed after 60 events. Evaluation of time-to-progression as primary endpoint (TTP) will be performed at 120 events. Secondary endpoints are number of patients reaching LTx, disease control rates, OS, progression free survival, quality of live, toxicity and safety.

**Discussion:**

As TACE is the most widely used primary treatment of HCC before LTx and sorafenib is the only proven effective systemic treatment for advanced HCC there is a strong rational to combine both treatment modalities. This study is designed to reveal potential superiority of the combined TACE plus sorafenib treatment over TACE alone and explore a new neo-adjuvant treatment concept in HCC before LTx.

## Background

Hepatocellular carcinoma (HCC) is the sixth most common cancer worldwide with more than 1 million deaths annually [1]. The prevalence of Hepatitis B and C with consecutive liver cirrhosis and HCC tumor growth leads to an increasing incidence of HCC especially in Europe and the USA [2]. HCC develops in a cirrhotic liver in 80% of cases, with an annual incidence of 2–6% for hepatitis B virus carriers and 3–5% for hepatitis C virus infected individuals. Two decades ago, the prognosis of HCC was devastating with most patients dying within the first year after diagnosis irrespective of their treatment [3]. The development of standardized surveillance strategies and the introduction of the Barcelona-clinic liver cancer classification (BCLC) for clinical management of HCC have significantly improved outcome. In industrialized countries 30–40% of patients are now being diagnosed at initial stages when curative treatments can be optimally applied. 5-year overall survival (OS) after resection, liver transplantation (LTx) or percutaneous treatment in select candidates reaches 50% to 70% in patients with early HCC (single or 3 nodules ≤3 cm) [1]. Untreated patients at an intermediate stage (multinodular asymptomatic tumors without an invasive pattern) achieve a median OS of 16 months. Locally ablative treatments provide good results (5-year survival 40–50%) for these patients but cannot achieve response rates and outcomes comparable to surgical therapy, even when applied as a first line treatment.

LTx is the best treatment option for patients with small multinodular tumors or those with advanced liver dysfunction. It has the potential to cure the tumor and the underlying liver disease. Tumor size at the time of LTx as defined by the Milan criteria (single tumors ≤5 cm or 3 nodules ≤3 cm) has been established as a prognostic factor [4]. In tertiary referral centers applying these criteria, survival is ~70% at 5 years, with a recurrence rate of less than 15% [5]. The shortage of donors still curtails the potential benefits of LTx. In western countries, tumor progression occurs in 20–50% of cases on the transplant waiting list.

Transarterial chemoembolization (TACE) is the most widely usedneo-adjuvant treatment for HCC patients listed for LTx. Results of randomized controlled trials and meta-analyses of pooled data for patients with non-resectable HCC show a clear survival benefit after TACE compared with conservative management, and is therefore considered as standard of care in non-resectable HCC [6]. Two studies using TACE for bridging to LTx reported excellent outcomes [7,8]. Nevertheless, only patients with preserved liver function and asymptomatic multinodular tumors without vascular invasion or extrahepatic spread are eligible for TACE to avoid hepatic failure and severe adverse events [9]. Radiofrequency ablation was not considered because only few heterogenous uncontrolled studies suggested a slightly decrease in drop-out rate in patients treated with RFA before LTx and there is the risk of needle tract metastases.

Since HCC is generally considered to be chemoresistant, results of systemic therapy have previously been disappointing. Tumor response rates for single or multiple agent chemotherapy regimens were low without durable remission leading to a 1-year survival between 0% to 30% [10]. Increasing knowledge on the molecular pathogenesis of HCC has lead to the development of molecular targeted therapies. The oral multikinase inhibitor sorafenib (Nexavar^®^) blocks angiogenesis and cell proliferation in HCC. In patients with advanced HCC, sorafenib has shown a significant improvement in time-to-progression (TTP) and OS [11,12]. After the drug has now been approved by both, FDA and EMEA, it is the new reference standard treatment of patients with advanced HCC [12].

Evidence-based treatment for HCC relies on fewer than 100 randomized controlled trials and many observational studies. LTx with previous bridging by TACE is now accepted as the only treatment capable of definitely curing HCC but can only be applied to less than 30% of patients. Low response to TACE and progression on LTx waiting list are the major prognosis limitating factors. Sorafenib has direct inhibitory effects on tumor growth and maintains stable disease in many HCC patients. The combination of TACE and sorafenib represents a logical, new and encouraging approach for neo-adjuvant HCC therapy before LTx.

## Design

### Subject recruitment

The final protocol has been approved by the local ethics committee of the Ruprecht-Karls University of Heidelberg, Faculty of Medicine (EudraCT-Nr.: 2008-002269-29). The medical secrecy and the Federal Data Protection Act will be followed. Written informed consent has to be obtained. 208 patients (male or female) over 18 years of age with HCC (single nodule -8 cm or maximum of 3 nodules ≤3 cm) without extrahepatic disease potentially eligible for LTx will be enrolled in the study. Recruitment will start in October 2008. Patients are considered for recruitment to the study according to inclusion and exclusion criteria (Table 1).

**Table 1 T1:** Criteria for inclusion and exclusion of patients

**Inclusion criteria**	**Exclusion criteria**
• Men and women >18 years of age	• Prior systemic anticancer therapy or local tumor therapy (i.e. LITT; PEI, cryotherapy, RFA, TACE)
• HCC (single nodule -8 cm or max. 3 nodules ≤3 cm) diagnosed by histology or non-invasive EASL criteria	• Significant cardiovascular disease such as myocardial infarction < 6 months previously, chronic heart failure (revised NYHA grade III-IV) or unstable coronary artery disease
• Baseline CT or MRI and bone scan without evidence of radiologically definable major vascular invasion or extrahepatic disease	• Extrahepatic disease, portal vein or other major vascular involvement;
• Hb >9.0 g/%, WBC >3.000 cells/mm^3 ^(ANC >1.500 cells/mm^3^), platelets >75.000 cells/mm^3^, bilirubin <3 mg/dl	• Uncontrolled hypertension despite optimal management
• Karnofsky index >70%	• Thrombotic or embolic events including transient ischemic attacks within the past 6 months
• Bilateral renal function with serum creatinine <1.5 mg/dl	• Hemorrhage/bleeding event = Grade 3 within 4 weeks of first dose of study drug
• INR/PTT < 1,5 × upper limit of normal	• Patients with previous malignancy other than carcinoma in situ of the skin and the cervix within the past 5 years prior to treatment
• Written informed consent	• Pregnant or breastfeeding patients.
	• Patients with uncontrolled infections or HIV seropositive patients
	• Mental conditions rendering the patient incapable to understand the nature, scope, and consequences of the study. No patient will be enrolled in this study more than once
	• Prior organ transplant (e.g. renal Tx)
	• Concomitant immunosuppressive treatment (before LTx)
	• Patients not eligible for LTx. Severe pulmonary disease that would be hazardous for LTx

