### Data safety monitoring board

An independent data safety monitoring board (DSMB) monitors closely the proper conduct of the trial and all SAE reports to ensure the safety of the subjects during the course of the study. This committee consists of three independent physicians (2 surgeons, one oncologist) as well as a biometrician and decides on the final diagnostic classification of critical clinical events. For all serious adverse events, the documentation and relevant patient data are verified by the coordinating personnel before submitting the data to the Adverse Events Committee for diagnostic classification. Analysis of safety related data is performed with respect to frequency of:

• Serious adverse events and adverse events stratified by body-system

• Adverse events stratified by severity

• Adverse events stratified by causality.

Patient toxicities will be assessed using the NCI Common Toxicity Criteria (CTC-AE V3.0). Toxicity will be evaluated pretreatment, bi-weekly during the first month, every four weeks during the following time of treatment and at follow-up. Unacceptable toxicity is defined as unpredictable or irreversible Grade 4 toxicity. Decisions regarding sorafenib treatment and dose-adjustment will be made using the guidelines of the actual sorafenib prescribing information.

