### Study design

The HeiLivCa trial is a prospective, multi-center, placebo-controlled, randomized, double-blind clinical trial with two parallel treatment groups receiving TACE plus sorafenib or TACE plus placebo. Patients in both groups will be treated with a maximum of four TACE procedures. For TACE carboplatin will be used as chemotherapeutic drug and lipiodol as embolizing agent. Four weeks after TACE, response will be evaluated by CT-imaging. Study medication will be stopped at progression. For patients without progression, treatment with sorafenib or placebo will be continued until LTx. All patients will be followed for 24 month after end of treatment. The duration of the overall trial is expected to last approximately 48 months. The actual duration of trial may vary due to the availability of patients meeting the criteria after registration for LTx. (Figure 1)

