### Investigation schedule and follow-up

Pre-treatment evaluation for all patients includes demographic data, medical history, physical examination, co-morbidities, and concomitant medications, complete lab (CBC, hemoglobin, hematocrit, sodium, potassium, magnesium, calcium, chloride, BUN, creatinine, ASAT, ALAT, GGT, alkaline phosphatase, total bilirubin, direct/indirect bilirubin, lipase, amylase, lactat dehydrogenase, total protein, albumin, glucose, bicarbonate, autoantibodies, PTT, PT and INR, tumor marker AFP, hepatitis virology, TSH, fT3 and fT4) and radiological studies to meet the inclusion criteria. During treatment, patients will visit the outpatient clinics every two weeks during the first month and every four weeks thereafter. At this visits the aforementioned laboratory measurements, physical examination, concomitant medication, vital signs, Karnofsky status and adverse events will be recorded in the electronic case report form (eCRF). During each monthly visit, patients will be provided with the required monthly amount of study product (or placebo) and are asked to return the emptied study boxes to survey compliance. Four weeks after each TACE imaging study, a CT scan of the thorax and abdomen as well as analysis of tumor marker AFP will be performed. At end of treatment due to progression or day of LTx, the aforementioned laboratory measurements, physical examination, concomitant medication, vital signs and adverse events will be recorded, imaging studies and AFP level analysis performed. In the first year after treatment, patients will be seen every 3 months for clinical assessment, laboratory analysis and imaging studies. Follow-up data of OS will be evaluated after 12 and 24 months after end of treatment or LTx.

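### Table 1 sets no albumin or ascites limit, so a narrow group of Child-Pugh class C candidates can qualify for TACE; one exclusion row would set a floor (minor safety point)

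*Protocol article*

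**What the plan says.** The Subject recruitment section makes Table 1 the entry rule: "Patients are considered for recruitment to the study according to inclusion and exclusion criteria (Table 1". Two of its inclusion rows limit liver function directly: "platelets >75.000 cells/mm^3^, bilirubin <3 mg/dl" and "INR/PTT < 1,5 × upper limit of normal". Platelets, creatinine, Karnofsky index and the mental-capacity exclusion bear on it only indirectly. No row mentions albumin, ascites, encephalopathy or a Child-Pugh class, and no such limit appears elsewhere in the article.

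Four other places matter:

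- Background, on TACE: "only patients with preserved liver function and asymptomatic multinodular tumors without vascular invasion or extrahepatic spread are eligible for TACE to avoid hepatic failure".
- Background, on transplantation: "LTx is the best treatment option for patients with small multinodular tumors or those with advanced liver dysfunction".
- Study design, on exposure: "Patients in both groups will be treated with a maximum of four TACE procedures". This is a ceiling, not a required number.
- Investigation schedule and follow-up: the pre-treatment laboratory list includes "total protein, albumin, glucose, bicarbonate" as well as bilirubin and INR, and a physical examination is planned.

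**The concern.** The Background gives preserved liver function as the condition that protects TACE patients from hepatic failure. Table 1 turns other parts of that sentence into rows: vascular invasion and extrahepatic spread are both excluded. Liver function is carried over only in part, through bilirubin and coagulation. A transplant candidate with low albumin and marked ascites is not stopped by either limit.

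The row excluding patients who are not eligible for LTx does not fill the gap, because the Background names advanced liver dysfunction as a reason to transplant. What is at stake is participant safety in both arms, since both receive TACE.

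**Working it through.** The plan states no figure on this point, so there is none to reproduce. The check asks which Child-Pugh scores Table 1 allows.

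**Assumed scale** (standard Child-Pugh, not given in the article), 1 / 2 / 3 points:

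- bilirubin <2 / 2–3 / >3 mg/dl
- albumin >3.5 / 2.8–3.5 / <2.8 g/dl
- INR <1.7 / 1.7–2.3 / >2.3
- ascites none / mild / moderate to severe
- encephalopathy none / grade 1–2 / grade 3–4

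Class A is 5–6 points, B is 7–9, C is 10–15.

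**What Table 1 allows.**

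- Bilirubin <3 mg/dl: 1 or 2 points.
- INR <1.5 × ULN: with an assumed ULN of 1.0 or 1.1 the limit is 1.5 or 1.65, so 1 point. With an assumed ULN of 1.2 the limit is 1.5 × 1.2 = 1.8, so 2 points become possible.
- Albumin and ascites: 1, 2 or 3 points each, as neither is limited.
- Encephalopathy: 1 point, or at most 2 if grade 1–2 is taken to pass the Karnofsky and mental-capacity rows.

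**Counterexample.** Bilirubin 2.5 mg/dl (2) + INR 1.4 (1) + albumin 2.7 g/dl (3) + moderate ascites (3) + no encephalopathy (1) = 10, class C. With the tumor, blood count, creatinine, Karnofsky, consent and remaining rows met, nothing in Table 1 excludes this patient. Improving bilirubin, albumin or ascites by one level gives 9 points, class B.

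**Enumeration of admissible profiles.** The strictest reading gives 2 × 1 × 3 × 3 × 1 = 18 profiles; the others multiply the INR or encephalopathy options by 2.

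| Reading | Profiles | A | B | C | Highest score |
|---|---|---|---|---|---|
| INR 1 point, no encephalopathy | 18 | 4 | 13 | 1 | 10 |
| INR 1 point, encephalopathy up to grade 2 | 36 | 5 | 26 | 5 | 11 |
| INR up to 2 points, no encephalopathy | 36 | 5 | 26 | 5 | 11 |
| INR up to 2 points, encephalopathy up to grade 2 | 72 | 6 | 48 | 18 | 12 |

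Class C is reachable on every reading. On the strictest, it needs bilirubin 2 to <3 mg/dl, albumin <2.8 g/dl and moderate or worse ascites together.

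**Effect of a class C exclusion.** The highest admissible score becomes 9 and no class B profile is removed. On the strictest reading 18 − 1 = 17 profiles remain, 13 of them class B, and 10 of those 13 include ascites.

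**The case against.** The strongest objection is that this is a condensed article. A fuller protocol, approved by the ethics committee, exists and may already contain a hepatic limit. That stands as a caveat. But Table 1 is presented as the recruitment criteria and goes down to neutrophil count, creatinine and HIV status, so a reader would expect a liver-function limit to be there.

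Second, Child-Pugh is an outside yardstick. True: the class label, the 10 points and the profile counts all depend on it. That albumin and ascites are unlimited does not.

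Third, a reader might infer that Table 1 contradicts the Background. The documents do not support this. The Background sentence is general rationale and sets no threshold; it also speaks of multinodular tumors, whereas Table 1 expressly admits a single nodule, so it cannot be read as a second entry rule. What remains is a mismatch between rationale and criteria.

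Fourth, clinicians see albumin, bilirubin and INR before the first TACE, and toxicity grading and DSMB review of SAE reports follow. These lower the risk but set no entry threshold. The stated decision guidance covers the drug, not the procedure: "Decisions regarding sorafenib treatment and dose-adjustment will be made using the guidelines of the actual sorafenib prescribing information".

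Finally, the example must combine three poor values and still pass the Karnofsky, platelet, creatinine and transplant-eligibility rows. This is fair, and it is why the gap is called narrow.

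**Conclusion.** The point holds as a cheap improvement to participant safety, of minor weight. As written, Table 1 lets a narrow group of class C candidates enter and receive up to four TACE procedures, against the Background's rationale. The finding rests on the standard Child-Pugh scale, on an assumed INR ULN of 1.0 to 1.2, and on Table 1 being the full list of criteria.

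The size runs from 1 of 18 profiles to 18 of 72, depending on how INR and encephalopathy are read. These count score combinations, not patients. A reader might infer from them that a sizeable share of the 208 patients is affected, or that this is a major safety failure; the article gives no distribution of albumin or ascites and no hepatic event rate, so neither follows. Nor is any bias, loss of power or effect on the analysis claimed.

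**What to change.** Add one exclusion row to Table 1: *Child-Pugh class C (10 points or more) at screening*, scored before randomization from the bilirubin, albumin and INR already on the pre-treatment list and from the physical examination. If the full protocol already has such a limit, show it in Table 1.

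The row is a minimum floor. It does not by itself secure preserved liver function, because class B patients with ascites stay eligible. Whether to set a tighter limit within class B is the sponsor's clinical choice; nothing in the article selects a cut-off.

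Cost: no new laboratory test and no change to the analysis or sample size. Ascites and encephalopathy must be graded at the screening examination, which the article lists without naming them. A small number of class C candidates, which the article does not allow one to quantify, would be lost.

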### Trial coordination

The trial is coordinated by the Department of Surgery at the Ruprecht-Karls-University, Heidelberg, Germany in cooperation with the National Centre for Tumor Diseases (NCT), including overall trial management, trial registration (International Standard Randomized Controlled Trial Number (ISRCTN24081794, ), database management, quality assurance including monitoring, reporting and the scientific program of all trial related meetings.

### Data safety monitoring board

An independent data safety monitoring board (DSMB) monitors closely the proper conduct of the trial and all SAE reports to ensure the safety of the subjects during the course of the study. This committee consists of three independent physicians (2 surgeons, one oncologist) as well as a biometrician and decides on the final diagnostic classification of critical clinical events. For all serious adverse events, the documentation and relevant patient data are verified by the coordinating personnel before submitting the data to the Adverse Events Committee for diagnostic classification. Analysis of safety related data is performed with respect to frequency of:

• Serious adverse events and adverse events stratified by body-system

• Adverse events stratified by severity

• Adverse events stratified by causality.

Patient toxicities will be assessed using the NCI Common Toxicity Criteria (CTC-AE V3.0). Toxicity will be evaluated pretreatment, bi-weekly during the first month, every four weeks during the following time of treatment and at follow-up. Unacceptable toxicity is defined as unpredictable or irreversible Grade 4 toxicity. Decisions regarding sorafenib treatment and dose-adjustment will be made using the guidelines of the actual sorafenib prescribing information.

### Medication supply

The chemotherapeutic agent for TACE is prepared and provided by the pharmacy of each study center. Sorafenib and the placebo are prepared and supplied by Bayer Health Care GmbH and packaged and labeled for the trial by the pharmacy of the University Hospital Heidelberg.

### On site monitoring

The study is performed according to the principles of the ICH-GCP consolidated guidelines as required by regulatory agencies and the ethical principles according to the current revision of the Declaration of Helsinki and local legal and regulatory requirements [13,14]. The trial is monitored by KKS Heidelberg according to their standard operational procedures based on ICH-GCP guidelines.

### Study design

The HeiLivCa trial is a prospective, multi-center, placebo-controlled, randomized, double-blind clinical trial with two parallel treatment groups receiving TACE plus sorafenib or TACE plus placebo. Patients in both groups will be treated with a maximum of four TACE procedures. For TACE carboplatin will be used as chemotherapeutic drug and lipiodol as embolizing agent. Four weeks after TACE, response will be evaluated by CT-imaging. Study medication will be stopped at progression. For patients without progression, treatment with sorafenib or placebo will be continued until LTx. All patients will be followed for 24 month after end of treatment. The duration of the overall trial is expected to last approximately 48 months. The actual duration of trial may vary due to the availability of patients meeting the criteria after registration for LTx. (Figure 1)

